### Anthropometry and blood pressure measurements

Height will be measured to the nearest 0.5 cm by a measuring tape mounted on the wall while the individual stands in a standing position without shoes. Waist circumferences will be measured to the nearest 1 cm using a non-stretchable measuring tape using a standard method [34]. Weight measurement and body composition analysis (% fat mass, % fat-free mass, and visceral fat) will be performed via a bioimpedance analyzer (InBody, model 770, Seoul, South Korea) while participants are with minimal clothes and not wearing shoes or stockings. Systolic and diastolic blood pressure (SBP and DBP) will be measured at the beginning and end of intervention periods after 5 min of rest when participants are in the sitting mode, for the right arm, using a sphygmomanometer (Riester Diplomat-presameter, Jungingen, Germany) (Table 1). All measurements will be performed 3 times at each visit (at the beginning and the end of each intervention phase) and their mean value will be recorded as the final value.

### Physical activity and dietary intake assessment

The participants will be asked to keep their physical activity level and dietary intake constant during the study. The participant’s physical activity will be assessed using 3-day physical activity records (2 weekdays and 1 day of the weekend). The 3-day physical activity records will be filled in 6 times during the study (at the beginning and end of each intervention phase) (Table 1). The recorded data will be converted into metabolic equivalent-min/day (MET-minute/day) using the updated version of the compendium of physical activities [35]. Three-day dietary recalls (2 weekdays and 1 day of the weekend) will be used to measure dietary nutrient intake, including macro and micro-nutrients, at the beginning and the end of each phase of the intervention.

### Blood samples

After an overnight fast (10–12 h), venous blood samples (15 mL) will be taken from participants between 7:00 and 9:30 a.m. at the beginning and end of each phase (Table 1). Then blood samples will be aliquoted to 2 serum samples, 1 plasma sample, 1 buffy coat sample, and 1 whole blood sample in DNase- and RNase-free 1-mL microtubes and will be stored at − 80 °C until analysis. Serum samples collected at the beginning and the end of each phase will be used for biochemical analyses.

### Laboratory assessment

Fasting serum glucose, serum TG, HDL-C, TAC, TOS, MDA, MPO, NO, the enzyme activity of SOD, CAT, GPX, and GR will be determined from serum samples using available standard kits.

### Compliance

The intervention oils will be provided for the participants and their families. We will ask participants to bring back intervention oil bottles provided in the previous visit. Then, these bottles will be weighed. Furthermore, 3-day dietary recalls will be used to assess the compliance of the participants to the intervention protocol.

### Assessment of medication use

Participants will be recommended to maintain their medication use during the study period. The researchers will also ask participants to inform them regarding the use and/or change of any medications during the study period since some drugs might have an impact on biochemical markers. To track their medication use, participants will be asked to bring all medications they consume during the intervention period at each visit. We will also ask them to report their usual medications (with their dosage) when contacted to assess the dietary intake data (Table 1).

### Assessment of adverse events and provisions for post-trial care

We anticipate that the intervention oils will have no harm or adverse effect on the participants. However, adverse events, if any, will be reviewed by the trial steering committee and reported to the ethics subcommittee for monitoring the clinical trials at Shahid Sadoughi University. After completing the intervention periods, the blood test results, assessment of food intake, and physical activity will be interpreted for the participants and necessary recommendations will be provided if needed.

### Data management

Data collection, coding, and entry will be done manually by the research staff for the study. Data will be kept by the principal investigator ([name]) of the research. Each study participant will be allotted a study code number and identifying information of study participants will be accessed by authorized personnel. Access to protocol, dataset, and statistical code will be available on reasonable request by the corresponding author.

### Statistical analyses

The statistical analysis will be performed using STATA software (version 14, TX, 77,845 USA). The normal distribution of the quantitative data will be determined using the Kolmogorov–Smirnov test, and the skewed variables will be normalized by transformation before analysis. The effects of treatment oils will be compared using the linear mixed method with the rolling process between-subject factors. Effect sizes will be adjusted by the potential confounders including age, sex, baseline BMI, the number of intervention oils consumed per subject, physical activity as metabolic equivalent-min/day, and the amount of calorie intake as covariates. Also, we will be performed subgroup analysis for sex. We will use the intention-to-treat method to handle protocol for those with non-adherence. No interim analysis is planned for this study because no early confirmatory conclusion of the effect of intervention oils can be drawn before the end of the study and enrollment of all participants. To control the carryover effect, clinically, an appropriate washout period will be considered (1 month). However, the carry-over effect will also be statistically tested through the mixed effect model. Any missing data will be handled using multiple imputations according to Harrell’s guidelines [36].

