### Sample size

The sample size required to investigate and compare the outcomes of the study between the three groups was calculated by considering these items: due to the limited literature regarding the impact of *Pistacia atlantica* on antioxidant capacity in humans and citing the calculations from researcher’s own experiences about similar oils, the minimal effect size of 0.10–0.13 as a conservative average was considered for primary outcomes [30]. Also, a correlation between repeated measures as a conservative average was considered 0.5. The power and confidence interval for these calculations were considered as 0.80 and 0.95, respectively. Calculations were done using GPower 3.1.4.9. Therefore, the sample size for each treatment oil period was estimated to be 21 subjects; with taking a 10% of dropout, we required at least 24 people for each intervention period. Based on this calculation, 72 eligible participants will be entered into the current study. We will also calculate the power of this trial using a conservative estimate of a medium effect size.

Due to the limited literature regarding the impact of *Pistacia atlantica* on antioxidant capacity in humans and citing the expert’s opinion, the effect size [standardized mean difference (SMD)] was considered to be at least one. Based on this, considering the first type error of 5% and power of 80% and using the table of sample sizes calculated for factorial studies [31], the sample size in each group was estimated to be 21 subjects, which takes into account the 10% drop, requires at least 24 people in each intervention period. Based on this calculation, 72 eligible participants will be entered into the current study.

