### Primary and secondary outcomes

The primary outcomes will be changes in serum total antioxidant capacity (TAC) and total oxidant status (TOS), malondialdehyde (MDA), nitric oxide (NO), the enzyme activity of myeloperoxidase (MPO), superoxide dismutase (SOD), catalase (CAT), glutathione peroxidase (GPX), and glutathione reductase (GR). We will use standard ELISA kits for the measurements. Mean difference ± SD values from the baseline will be reported. The time-point for intervention periods will be 8 weeks. The secondary outcomes will be changes in body weight and body composition measurements (waist circumference, hip circumference, total body fat mass, muscle mass, visceral fat mass), as well as, blood pressure, fasting serum glucose levels (FBG), systolic and diastolic blood pressure (SBP and DBP, respectively), serum triglyceride levels (TG), and high-density lipoprotein cholesterol (HDL-cholesterol).

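### A Kolmogorov–Smirnov test on the outcome variables, not a scale fixed in advance, decides whether each of the nine primary markers is transformed

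*Protocol article*

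**What the plan says.** The Statistical analyses section gives a two-step rule. First, "The normal distribution of the quantitative data will be determined using the Kolmogorov–Smirnov test"; then "the skewed variables will be normalized by transformation before analysis". The next sentence names the model: "The effects of treatment oils will be compared using the linear mixed method with the rolling process between-subject factors".

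Primary and secondary outcomes lists nine primary markers (TAC, TOS, MDA, NO, MPO, SOD, CAT, GPX, GR), defines them as changes, and adds: "Mean difference ± SD values from the baseline will be reported".

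The article does not say whether the test is applied to measured values or to changes, how many values enter it, whether the Lilliefors correction is used, or which transformation follows. Under Sample size, "72 eligible participants will be entered into the current study". Blinding, randomization, and allocation concealment keeps the oil codes A, B and C closed until the statistical analyses are done.

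**The concern.** The rule raises three difficulties.

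- **Wrong target.** A linear mixed model needs roughly normal residuals and participant effects, given oil, period and covariates. The marginal distribution of a variable is something else: men and women with different means can make it look non-normal when the residuals are fine. A step applied to variables before analysis cannot be a check of model residuals.
- **Weak instrument.** The standard Kolmogorov–Smirnov critical values assume that the mean and SD are known. If both are estimated from the same sample and no correction is made, the test is far too conservative.
- **Unsettled estimand.** A marker that passes is analysed as a difference in original units. One that fails is analysed on a transformed scale, where the model contrast is no longer the mean difference promised in the outcomes section. If the test is applied to changes, a log transformation is not even available, because changes can be negative.

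At stake are a primary result whose scale is settled by the data, possibly differently for each marker, and some power.

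**Working it through.** **Inputs from the article.** N = 72, which follows from its own steps: 21 / 0.9 = 23.3, rounded up to 24, and 24 × 3 = 72. Correlation between repeated measures 0.5, type I error 5%, power 80%. Table 1 gives six blood samples for these markers per person, so a marker yields 72 values at one visit, 72 × 3 = 216 end-of-phase values, or 72 × 6 = 432 in all. The article gives no figure for the normality test itself.

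**Assumption.** The article gives no SD or distribution for any marker. Log-normal markers with log-SD s from 0.2 to 1.0 were used. Skewness is (exp(s²) + 2) × √(exp(s²) − 1). For s = 0.5 this is (1.284 + 2) × √0.284 = 1.75.

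**Step 1: how often the test detects the skew (simulation).** Under normality the uncorrected test rejects about 0% of the time at a nominal 5%.

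| log-SD | skewness | uncorrected, 72 values | Lilliefors, 72 | uncorrected, 216 | uncorrected, 432 |
|---|---|---|---|---|---|
| 0.2 | 0.6 | 0.5% | 23% | 6% | 24% |
| 0.3 | 0.95 | 3% | 45% | 29% | 75% |
| 0.4 | 1.3 | 10% | 68% | 65% | 97% |
| 0.5 | 1.75 | 23% | 86% | 91% | about 100% |
| 0.6 | 2.3 | 44% | 95% | 99% | about 100% |
| 0.7 | 2.9 | 64% | 98% | about 100% | about 100% |
| 0.8 | 3.7 | 81% | >99% | about 100% | about 100% |
| 1.0 | 6.2 | 96% | 100% | about 100% | about 100% |

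A separate set of runs gave 24% in place of 23% at log-SD 0.5. Applied to 72 change scores, the uncorrected test rejected in 0.2%, 3% and 25% of samples at log-SD 0.3, 0.5 and 0.7.

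**Step 2: scale differing between markers.** As an illustration, take nine independent markers of identical shape, each with a 24% chance of being flagged. The chance that they do not all land on one scale is 1 − 0.24⁹ − 0.76⁹ = 1 − 0.000003 − 0.085 = about 92%. Correlation between markers would lower this.

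**Step 3: net power.** Cross-over contrast on end-of-phase values with subject, period and treatment effects, N = 72, correlation 0.5, effect set for 80% power on the log scale. The log is used when the test rejects. Each loss is log-scale power minus power with the test-selected scale, in percentage points.

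| log-SD | always log | always raw | uncorrected test, 72 (loss) | Lilliefors, 72 (loss) | uncorrected, 216 pooled (loss) |
|---|---|---|---|---|---|
| 0.3 | 80.0% | 77.9% | 77.9% (2.1) | 79.1% (0.9) | 78.4% (1.6) |
| 0.4 | 79.7% | 76.7% | 77.1% (2.6) | 78.6% (1.1) | 78.7% (1.0) |
| 0.5 | 79.5% | 73.7% | 75.4% (4.1) | 78.9% (0.6) | 79.3% (0.2) |
| 0.6 | 79.8% | 70.9% | 75.1% (4.7) | 79.4% (0.4) | 79.7% (0.1) |
| 0.8 | 79.0% | 62.8% | 75.7% (3.3) | 78.9% (0.1) | 79.0% (0.0) |
| 1.0 | 79.7% | 55.7% | 79.0% (0.7) | 79.7% (0.0) | 79.7% (0.0) |

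At N = 60 the largest loss with the uncorrected test was 79.3 − 72.8 = 6.5 points (log-SD 0.6).

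With change scores as the analysed outcome, N = 72 and the test run on the values, the loss was about 0 to 2 points (for example 79.8 − 77.8 = 2.0 at log-SD 0.5). If the test were run on the changes themselves it would hardly ever reject at that log-SD, so the loss there would approach that of always using the raw scale: 79.8 − 76.7 = 3.1 points.

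**Step 4: type I error.** The raw-scale analysis rejected true null effects in 4.8% to 5.6% of runs, against 4.9% to 6.3% on the log scale.

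**The case against.** The strongest reply is that the article leaves open almost everything on which the size of the problem depends. It does not say that measured values are tested, and it defines the outcomes as changes. It does not rule out the Lilliefors correction. Six measurements per person would allow 216 or 432 values, where even the uncorrected test finds moderate skew. A statistical analysis plan may settle the variant and the transformation, so their absence is no fault. All of this stands, and it limits the claim about size. It does not remove the stated rule: whichever variant is used, a test on variables picks the scale.

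A reader might infer that the plan misses most realistic skew and so loses much power. The article does not support that. It gives no marker distribution from which to call any skew realistic, and the low detection rates belong only to the uncorrected test on about 72 values. Nor is a large loss shown. The raw scale does badly at log-SD 0.8 (62.8% against 79.0%), but there the uncorrected test already flags 81% of samples. Power figures conditional on the skew being missed overstate what the whole procedure loses.

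Two further replies stand in part. The closed codes mean that the choice of scale cannot be steered by knowing which oil is which. And nothing in the article shows that every marker should be logged. That argues for naming the scale marker by marker, not for leaving it to the test.

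**Conclusion.** The point holds as a cheap improvement to the method. The stated rule makes the scale of each primary marker depend on a test of the wrong quantity. Markers of the same shape can be treated differently by chance, and a transformed marker no longer fits the promised mean-difference summary.

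The effect on power is modest: about 1 to 5 points at N = 72 for end-of-phase values if the test is uncorrected and run on about 72 values, and about 0 to 2 points with the Lilliefors correction or 216 pooled values. Type I error is not harmed. These sizes rest on log-normal markers with an assumed log-SD of 0.3 to 1.0 and on the article's correlation of 0.5. The case for change rests mainly on the unsettled scale and only secondarily on power.

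**What to change.** Delete the Kolmogorov–Smirnov step. State the analysis scale of each primary marker in advance: for example the log for positive-valued concentrations and activities that are typically right-skewed, with the start-of-phase value on the same scale as covariate. Check the mixed-model residuals, by plots, while the oils are still coded A/B/C. Give the other scale as a sensitivity analysis.

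This needs no extra participants, visits or assays. The price is in reporting: logged markers come out as ratios of geometric means, so the summary in Primary and secondary outcomes must be reworded for them. Moving from a change score to an end-of-phase value adjusted for the start-of-phase value also alters how the outcome is expressed and should be recorded as an amendment.

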## Methods and analysis

### Study design and population

This trial is a single-center, triple-blind, randomized, superiority, three-way cross-over clinical trial (RCT) among 72 patients with MetS. Eligible participants will consume a blend of *Pistacia atlantica* seed (20%) and canola oil (80%), a blend of corn (20%) and canola oil (80%) with TBHQ (75 ppm), and a blend of corn (20%) and canola oil (20%) without TBHQ after a 4-week run-in period. We aim to replace the oils regularly used at home with intervention oils. As all family members will receive the intervention oils, all data will also be collected for the spouses of the participants. The intervention periods will last 8 weeks and will be separated with 4-week washout periods in which sunflower oil will be provided for the participants. Sunflower oil is highly consumed among Iranian families as the main cooking oil [26]. The trial will be conducted in the Nutrition and Food Security Research Center, Shahid Sadoughi University of medical science, Yazd, Iran. We used standard protocol items for randomized trials (SPIRIT) as a framework for reporting this study protocol [27].

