### Blinding, randomization, and allocation concealment

The three intervention oils will be provided in the same shape, color, appearance, and odor and will be packed in the same bottles. Bottles will be blinded for researchers and participants and will be labeled with three codes (A, B, C) by an independent researcher. The codes will not be released until after the statistical analyses; therefore, neither the study participants nor the personnel nor the statisticians will be aware of the intervention oils. We do not anticipate any requirement for unblinding but if required, the trial manager and data coordinator will have access to group allocations and any unblinding will be reported.

We will use a stratified block (with a block size of 6) randomization in which the stratification will be done based on sex. Then, the participants in each block will be randomly assigned to one of the 6 sequences of the rolling process to consume the three intervention oils during the study period (ABC, ACB, BAC, BCA, CAB, or CBA; Fig. 1). To ensure that all the subjects receive treatments in a balance and random order, computer-generated random numbers will be used. The allocation sequence and randomization will be conducted by an independent researcher and will be concealed from the researchers. This will be done by putting the randomly assigned sequence of interventions for each participant in sealed opaque envelopes.

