### Trial status

The trial recruitment will begin on 22 May 2022. All trial participants should have finished the interventions up to 20 March 2023.

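### The stated crossover model names sequence but no period term, although the three periods fall in different seasons; any period effect can cost precision and, under one coding, make the carry-over test falsely positive

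*Protocol article*

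**What the plan says.** Study design and population describes a "triple-blind, randomized, superiority, three-way cross-over clinical trial (RCT) among 72 patients with MetS". Under Blinding, randomization, and allocation concealment, participants are "randomly assigned to one of the 6 sequences of the rolling process", that is, to one of the six possible orders of the three oils, in blocks of six. The rolling process is therefore the sequence.

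Statistical analyses then gives the model: "The effects of treatment oils will be compared using the linear mixed method with the rolling process between-subject factors". The adjustment covariates are "age, sex, baseline BMI, the number of intervention oils consumed per subject, physical activity as metabolic equivalent-min/day, and the amount of calorie intake". Of carry-over it says: "However, the carry-over effect will also be statistically tested through the mixed effect model". It does not say how carry-over will be coded. No period, visit, season or calendar-time term is named there or anywhere else in the article.

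On timing: "The intervention periods will last 8 weeks and will be separated with 4-week washout periods", after a 4-week run-in. Trial status puts the start of recruitment at 22 May 2022 and states: "All trial participants should have finished the interventions up to 20 March 2023". Primary and secondary outcomes defines the primary outcomes as changes, reported as differences from baseline.

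**The concern.** In a crossover trial each oil is given in different periods to different people, so period is a basic within-subject design factor. Sequence varies only between people and cannot stand in for it. The article goes as far as naming the between-subject factor, covariates that vary over time (physical activity, calorie intake) and a carry-over test, yet period is not among the terms.

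Two things are at stake. First, a shift common to everyone in a given period (season, diet, assay or storage time) that is not modelled is counted as residual noise, which widens the standard errors of the oil comparisons. Second, nobody has a previous oil in period 1. If the carry-over factor has a level for no previous oil, that level is the same thing as period 1, and without a period term the factor absorbs any difference between period 1 and the later periods.

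**Working it through.** **Plan's own figures.** The protocol gives no figure on this point. Its sample size reproduces and supplies N: a one-way comparison of three groups with a largest difference of 1 SD (f = 1/√6 = 0.408), 5% error and 80% power needs 21 per group; 21/0.9 = 23.3, so 24; 3 × 24 = 72.

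**Calendar.** Follow-up is 4 + 8 + 4 + 8 + 4 + 8 = 36 weeks = 252 days. From 22 May 2022 to 20 March 2023 is 302 days (43.1 weeks). The last possible entry is 302 − 252 = 50 days after the first, on 11 July 2022. If run-in starts at entry:

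| | Earliest start | Latest start |
|---|---|---|
| Period 1 | 19 June | 8 August |
| Period 2 | 11 September | 31 October |
| Period 3 | 4 December | 23 January |

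The ranges of start dates do not overlap, so period and season nearly coincide.

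**Precision.** Inputs: 72 people, 12 per sequence (72/6); total SD 1; correlation 0.5 (Sample size section), so the within-subject variance is 0.5. The shift d per period is an assumption, since the protocol gives none. Period means of −d, 0, +d add 72 × 2d² to the residual sum of squares. Without period the residual has 72 × 2 − 2 = 142 degrees of freedom, so

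residual variance = 0.5 + 144d²/142.

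- d = 0.25: 0.5 + 0.063 = 0.563; SE ratio √(0.563/0.5) = 1.06.
- d = 0.5: 0.5 + 0.254 = 0.754; SE ratio √(0.754/0.5) = 1.23 (1.22 if the small degrees-of-freedom term is ignored).

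For an illustrative case in which one oil differs from the other two by 0.3 SD (also an assumption), simulated power falls from 0.74 to 0.69 and 0.53. With period in the model it stays at 0.74–0.75.

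**Bias.** With all six orders equally represented and no missing data, oil and period are orthogonal. In simulation the oil test without period was not inflated. It became conservative: 0.034 at 0.25 SD per period and 0.012 at 0.5 SD, against a nominal 0.05.

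**Carry-over test.** Simulated false-positive rate with no true carry-over (72 people, correlation 0.5, 5% level; ranges show variation between simulation runs):

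| Shift per period | Previous oil vs none, no period | Differences among previous oils, no period | With period |
|---|---|---|---|
| 0 | 0.05 | 0.05 | 0.05 |
| 0.10 SD | 0.19–0.20 | 0.05 | 0.05 |
| 0.25 SD | 0.86–0.87 | 0.03–0.04 | 0.05 |
| 0.50 SD | 1.00 | 0.01 | 0.05 |

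**Change scores.** If the outcome is the change from each period's own baseline, a steady linear drift adds the same amount to every period and cancels; the shifts above then have to be read as shifts in the change. A seasonal cycle does not cancel. For an assumed cycle 0.3·sin(2πt/52), t in weeks from the start of period 1, the changes over weeks 0–8, 12–20 and 24–32 are +0.25, −0.10 and −0.27 SD. Their squared deviations from their mean sum to 0.14, which adds 72 × 0.14/142 = 0.07 to the residual variance. That gives SE +7% if the residual variance is 0.5, or +3.5% if it is 1 on the change scale. Other phases of the cycle give other values.

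**The case against.** The strongest reply is that the quoted sentence names only between-subject factors, while period is a within-subject factor. A condensed article may leave the full list of terms to an analysis plan, and nothing here excludes period. That stands as a caution: the text does not show that period will be omitted. It is still weak ground for leaving the sentence alone, because the article does state covariates that vary within a person and a carry-over test, and period is the one basic design term left out.

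The size of the problem also depends on choices that the protocol does not state, and these objections stand:

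- If sequence were crossed with oil, the oil-by-sequence cells would contain period. The residual variance then stays at 0.50 whatever the drift, at a cost of 10 interaction degrees of freedom instead of 2 for period.
- If carry-over were tested through the sequence factor, common period shifts would cancel; simulated rates were 0.047–0.050 at every drift tried.
- Linear drift cancels in change scores taken from each period's own baseline.
- At the protocol's own effect size of 1 SD, power remains above 99.9% even with the residual variance raised by half.

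A reader might infer more than the text supports: that the oil comparisons are biased, that their standard errors are certainly too wide, or that a spurious carry-over result would overturn the primary finding. With complete, balanced sequences there is no bias. The standard errors widen only if period effects exist on the analysed scale. Nothing in the protocol lets the carry-over test choose or replace the primary analysis. Bias through unequal late dropout is possible, since 10% dropout is allowed for, but it has not been quantified here, and multiple imputation is planned.

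**Conclusion.** The point holds in a conditional form. The model as written names sequence and covariates but not period, in a trial whose dates tie period closely to season. The 6% and 22–23% increases in standard error rest on an additive model, a residual variance of 0.5 and assumed shifts of 0.25 and 0.5 SD per period. The inflated carry-over rates rest, in addition, on coding carry-over as previous oil against none, which is one of several codings compatible with the text. Validity of the oil contrasts with complete data is not in question. What is exposed is precision and the meaning of a positive carry-over test. The article should be corrected on this, because the remedy is nearly free.

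**What to change.** State the model as fixed effects for oil (3 levels), period (3) and sequence (6), with a random subject effect and the listed covariates. State whether the outcome is the change from each period's own baseline. If carry-over is examined, add previous oil only to a model that already contains period, give its coding, report it as a sensitivity analysis, and say that it does not select the primary analysis.

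The cost is 2 degrees of freedom (residual 142 to 140 with complete data) and one sentence. No extra data are needed, since the period of every measurement is known from the visit schedule.
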